### Likely Rate of Loss to Follow-Up

An allowance has been made for just over 20% loss of participants to follow-up. To assist participants in attending the visits, reimbursement of costs for travel and parking will be offered in the form of gift certificates. The average of these would be Can $40.00.

### Number of Centers

A total of 2 sites within the same health region are required to meet the recruitment targets.

### Data Analysis

Data analysis will be performed on the outcome measures as follows:

The trial will meet Consolidated Standards of Reporting trials (CONSORT) requirements for reporting of randomized controlled trials. Baseline characteristics of patients in the 2 treatment groups will be reported using frequency distributions and descriptive statistics including measures of central tendency and dispersion.The changes in levels of nondegraded PDGF in CWF from the treatment and placebo treatment groups will be analyzed using repeated measures analysis of variance (ANOVA), using the wound type and treatment group as covariates.The changes in levels of proteases and endogenous growth factors in CWF from the treatment and placebo treatment groups will be analyzed using repeated measures ANOVA, with the wound type and treatment group as covariates.The percentage change in wound area after 4 weeks in the study will be assessed on an intention-to-treat basis using Student *t* test. On the basis of the percentage reduction in size at 4 weeks, the ulcers will be categorized as predicted to heal or not heal at 12 weeks. These healing predictions for the Promogran and placebo groups will be assessed by chi-squared analysis.The change in total protease status after application of the Promogran or the placebo will be assessed by chi-squared analysis.The change in healing status as determined by GMCSF biomarker after application of the Promogran or the placebo will be assessed by chi-squared analysis. Healing analysis will be performed on an intention-to-treat basis.All analysis will be completed using SPSS version 22 (IBM Corporation, Armonk, New York).

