### Primary Aim

The primary aim of this study was to determine whether the topical application of a protease inhibitor in combination with a topical growth factor prevents the degradation of applied growth factors in chronic VLUs and DFUs.

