### Outcome Measures

Primary outcome:

The difference in levels of nondegraded PDGF in CWF from the treatment and placebo treatment groups

Secondary outcomes:

The difference in levels of total protease and individual proteases in CWF from the treatment and placebo treatment groups as determined by enzyme-linked immunosorbent assay (ELISA) assayThe difference in levels of endogenous growth factors in CWF from the treatment and placebo treatment groups as determined by ELISA assayPercentage reduction in size of ulcers after 1 month of therapy and the proportion of VLU and DFU that are in a healing trajectory. In VLU, a wound area reduction of 40% within 4 weeks is predictive of healing at 12 weeks [67], and in DFUs, a wound area reduction of greater than 50% in 4 weeks is predictive of healing at 12 weeks [68]The presence of elevated total protease activity using WOUNDCHEK and the change with timeThe presence of a healing or nonhealing status as measured by GMCSF levels in CWF and the change with time as measured by ELISA assayThe completeness, ease of use, literacy, and timeliness of completing the pilot cost diary from a societal perspective. Both medical staff and participants will complete cost diaries

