### Measurement of Outcomes at Follow-Up Visits

At the first follow-up visit each week, the following will be performed:

The surface area of the wound will be traced and the area will be measured using the Visitrak device (Smith & Nephew).A photograph of the wound will be taken using a standardized protocol.A swab of the fluid on the surface of the wound will be taken using the WOUNDCHEK system to assess for elevated protease activity. The swabs will be stored for subsequent analysis of actual protease levels.A sample of wound fluid will be collected from the chronic wounds by covering the wound with a transparent occlusive dressing (Opsite, Smith & Nephew, Hull, UK) for approximately 1 hour. Fluid that has accumulated will then be aspirated and stored at −80°C. The wound fluid samples will be aliquoted into 20 ul samples and will be stored at −80°C. At the completion of the study, the samples will be analyzed using Quantibody analysis to measure the levels of proteases and nondegraded growth factors in the wound fluid, and a Western blot will be performed to assess rhPDGF-BB degradation. All of these samples will be assayed at the end of the study.

At the second visit in the same week, the following will be performed:

A sample of wound fluid will be collected.A swab of the fluid on the surface of the wound will be taken using the WOUNDCHEK system to assess for elevated protease activity.

At the third follow-up visit in the same week, the following will be performed:

Swab of the fluid on the surface of the wound will be taken using the WOUNDCHEK system to assess for elevated protease activity.The cost diary for that week will be completed.

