### Sample Size

One small study has assessed the levels of proteases in CWF from VLU after the application of Promogran [43]. In that study, the reduction in elastase after 5 days was approximately 80%, and the reduction in MMP-9 was approximately 45%. There are no data on the degradation of rhPDGF-BB that is applied topically to VLU or DFU. For the sample size analysis, a modest reduction in protease levels of 25% was estimated. Due to the variability of factors, an SD of 35% of the value for the control levels was used. Using a power of 80% and a 5% level of significance, the calculated sample size was 31 in each group. Due to possible nonadherence with the study and collection of samples, the number of participants to be recruited is 40 in each group.

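### The primary PDGF outcome is a between-group difference but the analysis is of changes over time, and the deciding ANOVA term and the role of the two gel-only weeks are not stated

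*Protocol article*

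**What the plan says.** - **Outcome Measures.** The primary outcome is "The difference in levels of nondegraded PDGF in CWF from the treatment and placebo treatment groups". No time point or summary over time is attached to it.
- **Data Analysis.** What is analysed is the change in nondegraded PDGF levels in the two groups. These changes "will be analyzed using repeated measures analysis of variance (ANOVA), using the wound type and treatment group as covariates". The section does not name the term that decides.
- **Planned Interventions.** Everyone receives the growth factor gel alone for two weeks, to supply baseline growth factor and protease levels. The randomised dressing is then added for four weeks. Whether the two baseline weeks enter the ANOVA as time levels is not stated.
- **Sample Size.** The calculation is one two-group comparison of protease levels: "a modest reduction in protease levels of 25% was estimated", and "an SD of 35% of the value for the control levels was used". It gives the power (80%) and significance level (5%) for a formal test, but does not identify the PDGF test.
- **Measurement of Outcomes at Follow-Up Visits.** Quantibody measures nondegraded growth factors; in addition, "a Western blot will be performed to assess rhPDGF-BB degradation".

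**The concern.** A difference in levels between groups is naturally tested by the between-subject group term. A change in levels that differs between groups is tested by the group-by-time term. The planned model produces both, and the two sections point to different ones.

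The two terms answer different questions. If all six weeks are in the model, the group term averages over two weeks in which the arms are treated alike, which dilutes any dressing effect. The group-by-time term does pick up the shift from gel-only to dressing weeks. However, as an omnibus test it spreads that one comparison over five degrees of freedom and also reacts to any other divergence in time pattern.

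Two things are at stake: missing a real effect by relying on the weaker term, and leaving room to choose between terms after unblinding.

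**Working it through.** **1. The plan's own figure.** Inputs from Sample Size: difference 25, SD 35 (both as % of the control level), power 80%, significance 5%, taken as two-sided.

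n per group = 2 × [35 × (1.960 + 0.842) / 25]² = 30.8, so 31.

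The stated 31 reproduces (one-sided 5% would give 25). The sample size arithmetic is not in question here.

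**2. Assumptions for the comparison of terms.** The article says no data exist on degradation of topically applied rhPDGF-BB, so these are illustrative:
- 25% effect and 35% SD carried over from protease to PDGF
- 31 analysed per group
- one sample per week, six weeks, with an effect of 0, 0, 25, 25, 25, 25
- compound symmetry with within-person correlation ρ = 0.5, varied from 0.3 to 0.7
- wound type not modelled

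**3. Group term over six weeks, ρ = 0.5.**
- Mean difference = 25 × 4/6 = 16.67
- SE = √{2 × 35² × [0.5 + 0.5/6] / 31} = 6.79
- Ratio = 16.67/6.79 = 2.45, giving power of about 69% by the normal approximation and 68% by the noncentral t with 60 df. Simulation (4,000 trials) gave 67%.

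**4. Group-by-time term, ρ = 0.5.**
- Sum of squared deviations of the weekly effects from 16.67 = 2 × 16.67² + 4 × 8.33² = 833.3
- Noncentrality = (31/2) × 833.3 / (35² × 0.5) = 21.1
- Power of the F test on 5 and 300 df = 96%. Simulation also gave 96%.

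**5. Disagreement.** Under these assumptions the two tests are nearly independent. The chance that exactly one is significant is 0.68 × 0.04 + 0.96 × 0.32 = 0.33; simulation gave 34%.

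**6. One-df contrast, mean of four dressing weeks minus mean of two gel-only weeks, ρ = 0.5.**
- SE = √{2 × 35² × 0.5 × (1/4 + 1/2) / 31} = 5.44
- Ratio = 25/5.44 = 4.59, giving power above 99% (99.5% by the noncentral t)

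**7. Range over correlation.** The first three columns are simulated. The last uses the step 6 formula with the noncentral t.

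| ρ | Group | Group-by-time | Disagree | 1-df contrast |
|---|---|---|---|---|
| 0.3 | 82% | 86% | 27% | 97% |
| 0.5 | 67% | 96% | 34% | 99% |
| 0.7 | 57% | >99% | 43% | >99% |

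**8. False positives.** With no true effect, if significance on either term were accepted: 1 − 0.95² = 0.0975. Simulation of the six-week model gave 0.095 to 0.098. This does not depend on the assumed PDGF effect, but it does depend on either term being allowed to count.

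**The case against.** **Drafting habit.** Proteases and endogenous growth factors show the same shift from differences (Outcome Measures) to changes (Data Analysis). Because the gel-only weeks exist to supply baseline data, the analysis sentence most naturally means change from baseline compared between arms. That is a fair reading, and it is the one the fix adopts. But the article does not state it, and the ANOVA as described does not deliver it as a single test.

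**SAP detail.** Coding of time and choice of contrast are often left to an analysis plan, which is not shown, and this is a condensed article on a proof-of-concept study. That would dispose of mere silence. Here two published statements about the primary outcome point to different terms, so an analysis plan could adopt either and still claim consistency.

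**Illustrative figures.** This stands. The effect and SD are protease assumptions, wound type is left out, and the schedule collects wound fluid at two visits a week rather than one.

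**Stronger readings to resist.**
- A reader might infer that the assay is open too, since the Primary Aim asks whether treatment "prevents the degradation of applied growth factors in chronic VLUs and DFUs" and a Western blot assesses degradation. The text does not support this. The outcome, the Quantibody measurement and the analysis all concern nondegraded levels, while the Western blot has no outcome and no analysis of its own. It is not a rival primary test.
- A reader might infer near-total conflict between the terms by analysing only the four dressing weeks, where a constant effect leaves group-by-time with no power. That means discarding baseline weeks collected for this purpose, against an analysis section that speaks of change.
- Nothing says the investigators would claim success on either term, so the 10% rate is conditional.

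**Conclusion.** The point holds as a clarification that should be made before unblinding. The outcome and analysis wording do not match, and neither the deciding term nor the place of the gel-only weeks is fixed. Under the illustrative assumptions, the choice between terms moves power from about 67% to about 96% at correlation 0.5 and changes the verdict in roughly a third of trials. Neither term is the best available test: a single contrast against the baseline weeks does better than both at correlations 0.3 and 0.5, and at 0.7 it matches group-by-time at above 99%. The inflation to about 10% is a risk only if either term may count; the documents do not show that it is planned. The percentages show that the choice matters and are not forecasts for this trial.

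**What to change.** Bring Outcome Measures and Data Analysis into line and name one deciding test. It should be the 1-df treatment-group contrast in mean nondegraded PDGF by Quantibody, averaged over the randomised-dressing weeks relative to the gel-only weeks, two-sided 5%, adjusted for wound type. State that the omnibus group-by-time test and the Western blot are supportive.

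This takes one or two sentences, written before unblinding. It needs no new patients, samples or assays, because the baseline weeks are already collected. The price is that a significant omnibus interaction or a favourable Western blot alone could not be reported as a positive primary result.

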### Planned Interventions

Participants will be randomized to receive a protease inhibitor or a placebo for 4 weeks of the study, in combination with a topical growth factor. All participants will receive just the topical growth factor for 2 weeks to obtain baseline data on growth factor and protease levels in the wound fluid.

The interventions patients will receive are as follows:

All participants will have Regranex gel (Smith & Nephew) containing a recombinant human PDGF for topical administration, applied to their leg or foot ulcers on a weekly basis for 6 weeks. Regranex is a nonsterile, sodium carboxymethylcellulose-based topical gel. Each gram of Regranex gel contains 100 g of rhPDGF-BB. This is applied by measuring a length of gel from a 15 g tube and is applied at a rate of 0.25 cm length of gel per cm^2^ of ulcer area. A maximum of 2 tubes will be used for each patient, and each patient will have his or her own treatment tubes to ensure that the limit of 2 tubes is not exceeded.Participants randomized to receive the protease inhibitor will receive Promogran (Johnson & Johnson) cut to the size of the ulcer and applied over the rhPDGF-BB.Participants in the placebo arm will receive Aquacel (ConvaTec) dressing applied in a similar manner to the Promogran. This dressing is very similar in appearance to Promogran and has no active protease inhibition function.VLU participants will have an absorbent pad and a 4-layer compression bandage system (Profore, Smith & Nephew) applied over the dressings.Diabetic foot ulcer participants will have an absorbent pad fixed with tape applied over the dressings.

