### Frequency and Duration of Follow-Up

Patients will be followed up 3 times in a week by a research clinical nurse for the treatment and by a blinded research nurse for outcome measurements (Table 1). The first visit could take up to 1.5 hours as wound fluid collection can be slow. The second visit would be scheduled within a 24-hour period and could take up to 1.5 hours for wound fluid collection. This visit would include the application of the protease inhibitor but not the growth factor. The third visit would require 45 min and it is not measurement visit. Table 1 contains the treatments and measurements at each visit for the each of the treatment weeks. There will be one final visit at the end of the last week of treatment.

At the first follow-up visit each week, the following will be performed:

The wound dressing will be taken down and the wound cleansed.The surface area of the wound will be traced and the area will be measured using the Visitrak device (Smith & Nephew).A photograph of the wound will be taken using a standardized protocol.The amount of rhPDGF-BB to be applied for that week will be calculated based on the ulcer size.A swab of the fluid on the surface of the wound will be taken using the WOUNDCHEK system to assess for elevated protease activity.A sample of wound fluid will be collected using a standardized methodology.The rhPDGF-BB will be applied to the wounds.The protease inhibitor dressing or the placebo will be applied.The secondary dressings will be applied.

At the second follow-up visit each week, the following will be performed:

Wound fluid will be collected.No measurements will be done; wound photography will be taken.The rhPDGF-BB will be applied to the wounds.The protease inhibitor dressing or the placebo will be applied.The secondary dressings will be applied.

At the third follow-up visit in the same week, the following will be performed:

No measurements, wound photography or fluid collection.The rhPDGF-BB will be applied to the wounds.The protease inhibitor dressing or the placebo will be applied.Secondary dressings will be applied.

**Table 1 table1:** Treatments and measurements at each study visit.

Day	Growth factor application	Protease inhibitor application	Wound fluid collection	Point of Careswab for total protease activity (WOUNDCHEK)
1	x	x	x	x
2	x	x	x	x
5	x	x		x

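### The primary repeated measures ANOVA would be better replaced by a mixed model that uses all available samples and takes the lead-in PDGF level as a covariate

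*Protocol article*

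**What the plan says.** The primary outcome (Outcome Measures) is "The difference in levels of nondegraded PDGF in CWF from the treatment and placebo treatment groups". Data Analysis gives its only stated analysis. There the variable is the change in that level rather than the level itself, and the method is stated in one clause: it "will be analyzed using repeated measures analysis of variance (ANOVA), using the wound type and treatment group as covariates". No other model term is named. The section does not say which samples enter or which term is the primary test. It names SPSS version 22 but no procedure. Intention-to-treat is stated for wound area and healing, not for PDGF.

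Planned Interventions provides a baseline: "All participants will receive just the topical growth factor for 2 weeks to obtain baseline data on growth factor and protease levels". It then sets the comparison period: "Participants will be randomized to receive a protease inhibitor or a placebo for 4 weeks of the study".

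The visit lists schedule wound-fluid collection at the first and second visit of each week. The protocol expects some of it to fail. Sample Size states: "Due to possible nonadherence with the study and collection of samples, the number of participants to be recruited is 40 in each group". The section on loss to follow-up allows for a little over 20%.

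**The concern.** Two features of the named method fit poorly with the trial's own design.

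- **Missing samples.** Classical repeated measures ANOVA needs a complete series for each participant. With 8 to 12 scheduled samples each, a small missing rate per sample removes many participants. If samples are missing for reasons linked to healing, the complete cases are also a selected group. That link is an assumption: the article says only that fluid collection can be slow.
- **Baseline.** Two weeks of lead-in are spent measuring each participant's PDGF level, but that level is not a covariate. Adjusting for it is, in large samples, never less efficient than ignoring it or subtracting it.

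At stake are precision and the number of analysable participants for the primary question. In addition, no single contrast is named as the primary effect estimate.

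**Working it through.** **Inputs from the article.** Effect 25% and SD 35% of the control value, both stated for protease levels; power 80%; significance level 5% (two-sided reproduces the result); 31 per group, raised to 40; two fluid samples per week; 2 lead-in weeks and 4 randomised-dressing weeks. The final visit is not counted, because no fluid sample is listed for it.

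**Inputs assumed.** Missing rate per sample p = 2%, 5%, 10%, independent between samples. Correlation between baseline and follow-up ρ = 0.3, 0.5, 0.7. The article gives neither.

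**1. The article's own figure.** n = 2 × [35 × (1.960 + 0.842) / 25]² = 30.77, so 31 per group. (The t-based version gives 31.8, so 32.) The allowance is 1 − 31/40 = 22.5%. Both stated figures reproduce.

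**2. Complete series.** Samples per participant: 4 weeks × 2 = 8 in the randomised period, or 6 weeks × 2 = 12 with the lead-in. The share with a complete series is (1 − p)^k.

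| p | k = 8: share | of 40 per group | k = 12: share | of 40 per group |
|---|---|---|---|---|
| 2% | 85% | 34.0 | 79% | 31.4 |
| 5% | 66% | 26.5 | 54% | 21.6 |
| 10% | 43% | 17.2 | 28% | 11.3 |

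The allowance is used up when (1 − p)^k = 31/40 = 0.775. This gives p = 1 − 0.775^(1/8) = 3.1% for 8 samples and p = 1 − 0.775^(1/12) = 2.1% for 12, if nobody is lost for any other reason.

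Falling below 31 does not by itself put power under 80%. The 31 is for a single comparison of two means, and averaging several samples per participant would need fewer. It does mean that the planned number of analysable participants is not reached.

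**3. Use of the baseline, with one baseline and one follow-up value.**

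- Follow-up value alone: 30.77, so 31.
- Change score: 30.77 × 2(1 − ρ).
- Baseline as covariate: 30.77 × (1 − ρ²).

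| ρ | Change score | Covariate |
|---|---|---|
| 0.3 | 43.07, so 44 | 28.00, so 28 |
| 0.5 | 30.77, so 31 | 23.08, so 24 |
| 0.7 | 18.46, so 19 | 15.69, so 16 |

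The covariate needs the fewest participants in every row. The gap to the change score is large at ρ = 0.3 and small at ρ = 0.7.

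**The case against.** Three stronger readings are tempting, and the article supports none of them.

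- **That participants with a missing sample are discarded by rule.** No such rule is stated. It follows only if the classical complete-case procedure is run. SPSS 22 also fits mixed models, and missing-data handling may sit in an analysis plan that is not shown. The increase from 31 to 40 was made partly for sample collection, so it already absorbs some of this loss. Real losses also cluster within participants, which leaves more complete series than independence implies.
- **That the baseline is wasted.** The analysis is of changes, and a change needs a reference. The lead-in may supply it, or may enter as earlier repeated levels. What stands is narrower: it is not a covariate, and a change score is the less efficient use of it.
- **That the planned test has very low power.** A reader could reach this by averaging raw levels over all 12 samples, lead-in included, with an effect only in the four second-visit samples of the randomised weeks. The article does not say which samples enter, and averaged raw levels are not changes. Under those same assumptions, at ρ = 0.5 with 31 per group, change from the lead-in mean (4 samples) to the randomised-period mean (8 samples) has about 89% power.

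That last reading also takes one side of a conflict over growth-factor application. Planned Interventions describes weekly application. The visit lists and Table 1 show it on days 1, 2 and 5. The narrative in Frequency and Duration of Follow-Up excludes it at the second visit. These places must be reconciled before any sample can be classed by its timing relative to PDGF.

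**Conclusion.** The point holds as a worthwhile improvement, not as a demonstrated failure of the trial. The article names a method whose classical form needs complete series, in a trial that expects incomplete ones. It omits as a covariate the baseline that it sets out to collect.

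If the classical procedure is used, about 3% (8 samples) or 2% (12 samples) missing per sample uses up the whole allowance. Naming the lead-in level as covariate would cut the number needed from 31 to between 28 and 16 per group over correlations of 0.3 to 0.7.

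The missing rates, their independence and the correlations are assumptions. The sample sizes in the baseline comparison are illustrative for PDGF: the article takes 25% and 35% from proteases and says that there are no data on degradation of the applied growth factor.

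**What to change.** Replace the repeated measures ANOVA with a linear mixed model, which SPSS 22 already offers:

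- **Data:** all available wound-fluid samples from the four randomised-dressing weeks, with all randomised participants included and none excluded for an incomplete series.
- **Terms:** treatment, week, treatment-by-week, visit within week, wound type, and the participant's mean lead-in PDGF level as covariate.
- **Primary contrast:** the treatment difference averaged over those four weeks, named as the single primary estimate.
- **Other markers:** the same model for proteases and endogenous growth factors, each with its own lead-in mean.

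Decide whether to limit the primary contrast to second-visit (day-2) samples only after the growth-factor schedule in Planned Interventions, Frequency and Duration of Follow-Up and Table 1 has been reconciled.

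The change needs no new participants, samples or software. The cost is revised wording and slightly more analysis work. Samples are assayed at the end of the study and analysed only then, so the change can be fixed in advance.

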### Randomization Method

Randomization will occur after the first week in which the participant’s compliance with optimal standard therapy is assessed. If the participant is not compliant at this point, he or she will not be randomized into the study. The research coordinator will randomly assign eligible participants using a computer-generated randomization tool. Following eligibility screening by the research coordinator, the system will generate a unique number. The research coordinator then telephones the treatment nursing staff and reports the number. In turn, treatment research nurses refer to a manual of unique numbers generated by an independent biostatistician before study activation to determine the study intervention allocated to the randomized patient. The randomization schedule will be stratified by wound type (VLU or DFU) in variable blocks of 4 and 6. Randomized patients will receive all treatments during the study period according to the intervention they were allocated. The patients, study investigators, research coordinator, laboratory technologists, and assessing research nurses will be blinded to the treatment allocation. Only the treating team members are not blinded.

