### Planned Subgroup Analyses

If the initial analysis demonstrates a difference between VLU and DFU responses to protease inhibitor application, subgroup analyses of these 2 groups will be performed.

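### Randomisation is stratified by wound type, but the healing and status tests ignore the stratum, and the treatment-by-wound-type term that the subgroup condition needs is not named

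*Protocol article*

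**What the plan says.** All references are to the Methods of the protocol article.

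- **Randomization Method:** "The randomization schedule will be stratified by wound type (VLU or DFU) in variable blocks of 4 and 6".
- **Outcome Measures**, cut-off for the first wound type: "In VLU, a wound area reduction of 40% within 4 weeks is predictive of healing at 12 weeks". The cut-off for the second type differs: "in DFUs, a wound area reduction of greater than 50% in 4 weeks is predictive of healing at 12 weeks".
- **Data Analysis**, area: the percentage change in wound area after 4 weeks "will be assessed on an intention-to-treat basis using Student" *t* test.
- **Data Analysis**, binary outcomes: "These healing predictions for the Promogran and placebo groups will be assessed by chi-squared analysis". Change in total protease status is handled the same way, and "The change in healing status as determined by GMCSF biomarker after application of the Promogran or the placebo will be assessed by chi-squared analysis".
- **Data Analysis**, PDGF, proteases and endogenous growth factors: the PDGF analysis is a "repeated measures analysis of variance (ANOVA), using the wound type and treatment group as covariates", and the other two use the same method and variables.
- The section on **planned subgroups** sets this condition for separate results: "If the initial analysis demonstrates a difference between VLU and DFU responses to protease inhibitor application, subgroup analyses of these 2 groups will be performed".

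**The concern.** Two things in the plan do not fit together.

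First, wound type is important enough to stratify the randomisation, to set separate healing cut-offs and to enter the ANOVAs, yet it is absent from the tests of area change, predicted healing, protease status and GMCSF status. When a stratum is balanced by design and then left out of the analysis, the between-stratum variation stays in the error term. The standard error is then too large for the design, the true type I error falls below 5%, and power is lost. In a trial of 40 per arm that loss can matter for the secondary healing aim.

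Second, separate VLU and DFU analyses are to follow only if the initial analysis shows that the two types respond differently to the protease inhibitor. That is a treatment-by-wound-type question. Main effects of treatment and wound type cannot answer it, and neither can a t test or chi-squared test without wound type. The Introduction treats the two types as different: the growth factor has shown significant benefit in DFU and not in VLU. A reader will therefore want both estimates.

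**Working it through.** **1. The plan's own sample size.** From Sample Size: difference 25, SD 35 (both as % of control level), power 80%, 5% significance, taken as two-sided.

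n per arm = 2 × (1.960 + 0.842)² × (35/25)² = 2 × 7.85 × 1.96 = 30.8, so 31. This agrees with the article. Going from 31 to 40 allows for 1 − 31/40 = 22.5% loss, which matches the stated allowance of just over 20%.

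The article gives no design inputs for wound area or healing, so the standardised effect 25/35 = 0.714 SD is borrowed from this protease calculation. The VLU/DFU mix, the stratum gaps and the odds ratio below are assumptions.

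**2. t test for area change (normal approximation).** With equal strata differing by D within-stratum SDs, the unadjusted standard error is inflated by k = √(1 + D²/4). The size becomes 2[1 − Φ(1.96k)] and the power about Φ(25/SE − 1.96k). At 31 per arm SE = 35 × √(2/31) = 8.89 and 25/8.89 = 2.81.

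- D = 0: power Φ(2.81 − 1.96) = 80.3%.
- D = 0.5: k = 1.031, size 4.3%, power 78.6%.
- D = 1: k = 1.118, size 2.8%, power Φ(2.81 − 2.19) = 73.3%, a loss of 7.0 points.

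**3. Simulation check.** Strata are equal (as near as 31 per arm allows) and balanced across arms. Chi-squared is compared with Cochran-Mantel-Haenszel (100,000 runs, assumed odds ratio 3.5), and the t test with a linear model that includes wound type (20,000 runs, effect 25, SD 35). Each cell shows unadjusted / adjusted.

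| Assumed stratum gap | N per arm | Type I error, % | Power, % | Loss, points |
|---|---|---|---|---|
| Healing 45% vs 36% | 40 | 5.3 / 5.3 | 78.7 / 78.7 | 0 |
| Healing 50% vs 30% | 40 | 4.7 / 4.9 | 77.0 / 77.2 | 0.2 |
| Healing 60% vs 20% | 40 | 3.3 / 4.9 | 65.8 / 69.9 | 4.1 |
| Healing 60% vs 20% | 31 | 3.5 / 5.1 | 54.2 / 59.5 | 5.3 |
| Healing 70% vs 15% | 40 | 2.1 / 5.1 | 49.7 / 62.7 | 13.0 |
| Area, 0.5 SD | 40 | 4.3 / 5.1 | 87.0 / 88.3 | 1.2 |
| Area, 1 SD | 40 | 2.8 / 5.0 | 83.0 / 88.1 | 5.1 |
| Area, 1 SD | 31 | 2.8 / 5.0 | 71.6 / 79.3 | 7.8 |

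For a one-SD gap at 31 per arm, the approximation and the simulation agree on a loss of 7 to 8 points.

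**4. Power of the subgroup condition.** Interaction SE = 35 × √(2/n_VLU + 2/n_DFU), with n per arm in each stratum. The assumed difference in effect is 25, the whole design effect (for example 25 in one type and 0 in the other).

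- 31 per arm, 50:50: SE = 35 × √(4/15.5) = 17.8; 25/17.8 = 1.41; power 29%.
- 40 per arm, 50:50: SE 15.7; power 36%.
- 80:20 mix: SE 22.2 and 19.6; power 20% and 25%.

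With a 50:50 mix, 80% power would need a difference of about 50 points at 31 per arm or 44 at 40 per arm. These figures use the single-comparison SD from Sample Size; repeated measurements could change that SD, but the article gives nothing from which to compute by how much.

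**The case against.** The strongest reply has five parts.

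- **The stratum is used where it matters most.** Wound type is in the primary PDGF analysis and in the protease and growth factor analyses. This stands: the point concerns secondary outcomes.
- **The unadjusted tests are valid.** A reader might infer that pooling two healing definitions biases the comparison or raises the false-positive rate. It does not. Allocation is balanced within wound type, so each arm has the same mix of definitions, and the error goes in the conservative direction. The two cut-offs are also type-specific predictors of the same event, healing at 12 weeks.
- **The loss may be nil.** The nearest rates in the Introduction are 45% of VLUs healing in 13 weeks and 36% of DFUs on placebo gel. At those rates chi-squared and Cochran-Mantel-Haenszel are equal. The larger gaps are assumed, and equal strata is the worst mix: at D = 1 with 80:20, k = √(1 + 0.16) = 1.077 rather than 1.118. This stands, although those two rates describe complete healing, not the 4-week prediction.
- **Baseline is not ignored.** Percentage change and change in status use baseline in their definitions. This stands; baseline area as a further covariate is optional.
- **The interaction may be intended.** Data Analysis names variables, not model terms, and a full-factorial ANOVA would contain the interaction. So one cannot say that the model lacks it, only that it is not named. The subgroup rule also does not mention statistical significance, so the article does not support the inference that VLU and DFU results would usually go unreported. It leaves undefined what would count as showing a difference.

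Separate estimates will indeed be imprecise. At 40 per arm and 50:50, the 95% half-width within one type is 1.96 × 35 × √(2/20) = 21.7 points. An interval shows that imprecision openly; a low-powered trigger does not.

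**Conclusion.** The point holds as a low-cost improvement to the secondary analyses. The named tests for area change, predicted healing, protease status and GMCSF status omit the randomisation stratum, which is inconsistent with the design and with the ANOVAs in the same section. The cost is efficiency only: nothing when the wound types have similar outcomes, 4 to 5 power points for a large gap at 40 per arm (up to 7 to 8 at 31 per arm for a one-SD gap), and about 13 for a very large one. All of these rest on assumed gaps and equal strata, and the area figures also on an effect size borrowed from the protease calculation.

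The subgroup condition needs a treatment-by-wound-type term that the described model does not name. If it is fitted, its power is about 20% to 36% for a difference equal to the design effect, so failure to show a difference would say little about whether VLU and DFU respond alike.

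None of this makes the tests invalid, undermines the primary analysis or changes the 31 or 40 per arm.

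**What to change.** - **Area change:** replace the t test with a linear model containing treatment and wound type. Log baseline area may be added as a further covariate.
- **Predicted healing, protease status and GMCSF status:** replace plain chi-squared with a Cochran-Mantel-Haenszel test or logistic regression stratified by wound type, keeping the type-specific healing cut-offs.
- **Interaction:** name the treatment-by-wound-type term in the model on which the subgroup rule depends, and say which analysis counts as the initial one.
- **Subgroups:** report VLU and DFU effects, and the interaction, with 95% confidence intervals whatever the interaction result, labelled as exploratory.

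The cost is a few sentences in Data Analysis and Planned Subgroup Analyses and some extra model lines. No new data, patients or visits are needed. The change should be fixed before unblinding.
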